## **12.0 Statistical Considerations**

To address missing data, we will examine the data for patterns of missingness and potential bias in missingness (SPSS Missing Values). If data are not missing at random, we will apply one of several available imputation methods in a sensitivity analysis based on the nature and extent of missing data. We will determine effectiveness using intention-to-treat principles with actual imputation of missing data. This will allow us to appreciate the potential biases inherent in a “real-world” setting due to drop out and poor adherence to study procedures.

Patients who share a single PCP might exhibit similarities that are not shared with patients attended by other PCPs. To address this, we will include random effects in the model for clinic site, PCP, and HC (though the small numbers of HCs may call for a fixed effect approach, or “insufficient replication”). To examine a stricter examination of effect, we will also do a “per protocol” analysis of complete cases. Completed cases will not be dependent on intermediate time point data collections (6 and 18 months). Potential selection bias will be corrected by including in our models covariates that are differentially related to study participation.

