## **1.0 Project Summary/Abstract**

Many African-Americans and Latinos with diabetes do not achieve recommended diabetes goals placing them at high risk for complications. Team-based models of care can help in reaching goals of therapy. Additionally, mobile health (mHealth) technologies can further improve outcomes among those more difficult to reach. This study will evaluate the impact of a team-based, mHealth intervention designed to improve medication adherence, healthy eating, and physical activity behaviors. We will compare this mHealth approach with usual care.

Clinical pharmacists and health coaches (HC) will deliver our proposed team-based intervention. mHealth delivery includes mobile phone text messaging, secure videoconferencing, and HC home visits. Pharmacists will focus on medication reconciliation and adherence. Health coaches will help identify psychosocial and environmental challenges to adherence in a culturally-sensitive manner. Together, they can assist in goal-setting, problem-solving, negotiation of competing priorities, and provide social support leveraging mHealth technologies.

Preliminary data from our research group supports the role of health coaches partnering with clinic-based pharmacists in improving diabetes outcomes in minorities. In the proposed mHealth intervention, patient-pharmacist videoconferencing will eliminate the need for in-person visits with a pharmacist, which is impractical for many low-income patients. In addition, our pilot work suggests that text messaging is a preferable means of communication and may facilitate more frequent contact with patients.

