## 5.0 Subject Enrollment

University of Illinois Hospital and Health Sciences System (UI Health) includes both inpatient and outpatient facilities serving a diverse population in Chicago. UI Health has 19 ambulatory centers staffed by Family Medicine and Internal Medicine PCPs and includes Mile Square FQHCs where care is provided independent of ability to pay. Four to six clinical sites will participate. All sites share access to the EMR, Cerner Powerchart, and employ clinical pharmacists through the UIC College of Pharmacy Practice.

We will employ the following recruitment/enrollment methods:

1. **Passive Advertising:** We will distribute study advertisement materials throughout UI Health, including clinical environments. Individuals will call research assistants (RAs) for eligibility assessment by phone.
2. **Active Recruitment from Registries:** The research assistants will work from a physician-approved list of patients with diabetes and A1c  $\geq 8$  identified from the electronic medical record. We will send letters informing patients that they may be eligible for the study and may opt-out of further contact. After one month, those who do not opt out will be contacted by the RAs to assess interest and eligibility.
3. **Active Recruitment in Clinical Sites:** On-site RAs will receive additional referrals directly from staff or patients interested in the study. In these situations, RAs will discuss the

study and assess eligibility in a private exam room within the clinic before or after a clinical encounter.

4. Diabetes Health Registry: RAs will call by phone individuals completing the Diabetes Health study (IRB 2011-0099) who indicated willingness to be contacted regarding future studies.

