#### mDAS - Pharmacist Component

1. Pharmacists will provide medication and disease management services to patients by following a Pharmacist Management Protocol (see attached).
2. The initial pharmacist videoconference will include medication reconciliation and review therapeutic goals.
3. Follow up videoconferences will occur every other month. The interval duration may increase/decrease based on individual preference and when subjects reach goals.
4. These subsequent visits will involve an evaluation of adherence, medication reconciliation, and a review of home glucose and/or blood pressure monitoring data, an evaluation of drug interactions and side effects, goal setting, basic lifestyle

modifications, pillbox use, development of a low-literacy medication list, and other adherence aids.

5. Pharmacists will adjust therapy according to the plan of care under PCP guidance and notify PCPs of agreed upon modifications through EMR notifications. Side effects will be conveyed to the PCP (if the PCP is not available, the covering physician will be contacted as per Pharmacist management Protocol).
6. Pharmacists will forward all electronic progress notes to PCP EMR "Inbox" after each encounter.
7. If the PCP feels that the patient should not remain in the study the provider can inform the Co-PIs to disenroll the participant.

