*Pharmacist Services.* Pharmacist services follow a standardized Pharmacist Management Protocol. All participating clinical sites have clinical pharmacists providing in-person disease management services and follow a similar protocol. All participating pharmacists have faculty appointments in the UIC Department of Pharmacy Practice. The UI Health system is a teaching hospital and as such, pharmacists at participating sites train an ongoing rotation of pharmacy residents and students. With the patient’s permission, residents and students may observe clinical consultations performed by the pharmacist. Residents and students will not provide any clinical care to patients and will not perform any videoconference visits. They will not have any role in this study. The clinical pharmacist reconciles medications during the first encounter with

assistance from the HC in the patient's home. Follow-up *mDAS* pharmacist activities include evaluation of medication and lifestyle adherence, reviewing home glucose and/or blood pressure monitoring log data, identifying therapeutic goals, formulating an approved plan of care, assessing for changes in medications, and documenting the plan in the EMR.

In addition, pharmacists provide education related to medication (name and purpose of medications; time, strength, and method of administration); drug interactions and side effects; goals of therapy; basic lifestyle modifications; and use of pillbox, low-literacy visual medication lists, or other adherence aids. Pharmacists educate and encourage lifestyle changes based upon ADA nutrition and physical activity guidelines. They propose medication changes based on algorithms and protocols derived from national guidelines under physician guidance. Pharmacists will have access to home glucose monitor readings during the videoconference, as well as ambulatory blood pressures obtained by the HC during home visits. Pharmacists will set the goals for A1c and blood pressure collaboratively with PCPs (e.g.,  $A1c \leq 7\%$ ) as is the case in regular clinical practice within our setting. These procedures are currently followed with clinical pharmacists in ambulatory management of complex patients with uncontrolled diabetes.

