Process evaluation will provide support for the project's potential as an intervention in a real-world setting. We will evaluate translation using the RE-AIM framework to determine dissemination potential and generalizability (Table 4). To assess adoption, we will conduct semi-structured interviews of providers, staff, and administrators, providing different perspectives.

Chain sampling will help identify those most likely to be “information rich” and continue until saturation reached.

Pharmacist interviews: Up to 15 pharmacists who have participated in the mHealth for Diabetes Adherence Support study (IRB 2016-0380) will be individually interviewed to gather feedback on delivering the intervention and potential for adoption.

An email invitation will be sent to pharmacists describing the purpose of the interview and a summary of the procedures. Interested pharmacists will be scheduled for one-on-one interviews with [name] or a research assistant. The interviews will take place in private room at the pharmacist’s clinical site or at a private campus location that is convenient for the pharmacist. A semi-structured interview guide will be used and content will focus on video conferencing, provider-pharmacist interactions, and interactions with health coaches. Interviews will be audio recorded. Names of the pharmacists will not be linked to their responses in order to maintain confidentiality. A brief demographic survey will be completed by the pharmacist and a number will be assigned to their interview. The interview will last approximately 30 minutes.

Interviews will be transcribed, coded and analyzed. Results will be used to inform the process evaluation component for the study (Aim 4) and future research involving clinical pharmacists, health coaches and the use of telehealth technology in health care.

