### **PROCEDURES**

#### **A. Appointment Scheduling**

- 1. New patients will be scheduled for an initial videoconference with pharmacist after health coach (HC) has completed at least one home visit with patient.
- 2. The HC will schedule the initial telehealth pharmacy visit within 90 days of a patient's enrollment in the study. Initial visits will be scheduled for 60 minutes. Scheduling will be done according to each recruitment site's preference.
  - a. Medication Therapy Management Clinic (MTMC): Visits will be scheduled in the electronic Medication Management Therapy Clinic (MTMC) appointment book in Cerner.

For instructions on scheduling, please refer to the MTMC Scheduling Guide (Appendix A). Appointment times will be based on patient room availability as well as the patient's and HC's availability. Only one research telehealth patient visit may be scheduled per half day (between the hours of 9am-12pm and 1pm – 4 pm. The pharmacist assigned to the patient at their initial visit will continue to see them for the duration of their time in the study, when possible.

- b. Mile Square: HC will forward a clinic note to the pharmacist with a message requesting an appointment. The HC will also text the pharmacist to alert them that a telehealth visit is needed. The pharmacist will work with the HC to find an agreeable time and will have that time blocked in the appointment book in Cerner.
  - c. Family Medicine (University Village) – HCs will schedule appointments directly with IRB approved pharmacists via encrypted email (preferred) or phone. Pharmacists will keep a separate calendar and block the time in their Cerner appointment book.
- 3. Subsequent visits will be scheduled by the pharmacist at each telehealth visit, based on the needs of the patient, as well as the availability of the patient and HC. These visits will be scheduled for a minimum of 30 minutes. However, visits with Spanish-speaking patients should be scheduled for 60 minutes to allow for translation.
- 4. Encounter cancellations will be made as soon as possible (*at least 24 hours prior to scheduled time*) when possible. The HC will call or text the patient the day before to confirm the visit. HCs may reschedule visits at the patient's request, but must work with the pharmacist to ensure their availability.

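### The planned random effects cover clinic site, PCP and health coach but not the clinical pharmacist, so the standard error of the mDAS effect would be too small if outcomes cluster by pharmacist

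*Protocol*

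**What the plan says.** Section 12.0 reasons that patients of one PCP may resemble each other, and answers that "we will include random effects in the model for clinic site, PCP, and HC". It adds that the coach may have to be a fixed effect because coaches are few. Later in the same section, subject is added as a random effect. No section adds a pharmacist term.

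On the pharmacist's part in the intervention, the protocol says:

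- Section 1.0: "Clinical pharmacists and health coaches (HC) will deliver our proposed team-based intervention".
- Section 6.1, mDAS - Pharmacist Component: "Pharmacists will adjust therapy according to the plan of care under PCP guidance".
- Section 6.4, on pharmacist services: "They propose medication changes based on algorithms and protocols derived from national guidelines under physician guidance".
- Pharmacy Management Protocol, part A, under the Medication Therapy Management Clinic (MTMC) item: "The pharmacist assigned to the patient at their initial visit will continue to see them for the duration of their time in the study". The sentence goes on to limit this to when it is possible.
- Section 12.0, pharmacist interviews below Table 4: "Up to 15 pharmacists who have participated in the mHealth for Diabetes Adherence Support study" are to be interviewed.

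In year 1 the usual-care arm gets a referral to a clinical pharmacist, not scheduled pharmacist sessions (section 6.0).

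**The concern.** mDAS has two kinds of deliverer. The plan models one of them, the coach, and leaves out the other, although its stated reason for modelling providers applies equally to the pharmacist. Patients who keep one pharmacist share that pharmacist's habits in adjusting therapy and supporting adherence, and these are plausible routes to A1c, blood pressure and LDL.

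The listed terms do not obviously stand in for a pharmacist term. Patients are randomised individually, in blocks within site, so each site and PCP intercept is shared by both arms and largely cancels from the arm contrast. A pharmacist effect that is present mainly under mDAS does not cancel. The coach term would absorb it only where coach and pharmacist go together. The documents suggest they need not: coaches are matched at least partly on culture and language, while pharmacists are booked through the clinics.

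If pharmacist variance exists and is not modelled, it enters the true variance of the mDAS mean but not the model's standard error. Confidence intervals would then be too narrow and the 0.05 level would not be held.

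**Working it through.** **The plan's own clustering figure.** The sample size justification in section 12.0 assumes an ICC of 0.01 with five clusters and reports a design effect of 1.34. With 20% drop-out, 220 × 0.80 = 176 completers, and 1 + (176/5 − 1) × 0.01 = 1.342. The figure reproduces. It enlarges the sample but does not change the standard error that the fitted model reports. The total of 220 is a separate matter; only the completer count is used below.

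**Inputs.**
- Completers per arm: 176/2 = 88.
- Two-sided alpha: 0.05 (section 12.0).
- Number of delivering pharmacists, k: not stated; 5, 10 and 15 are assumed.
- Pharmacist ICC, ρ: not stated. I use 0, 0.01 (borrowed from the plan's five-cluster value) and 0.05 (assumed).

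**Formulas.** Clustering is placed in the mDAS arm only:
- patients per pharmacist: m = 88/k
- design effect in the mDAS arm: DE = 1 + (m − 1)ρ
- true over reported standard error: R = √((DE + 1)/2)
- actual two-sided alpha: 2 × (1 − Φ(1.96/R))

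The SD of 1.8 cancels from R.

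| k | m | ρ | DE | R | Actual alpha |
|---|---|---|---|---|---|
| 15 | 5.9 | 0.01 | 1.049 | 1.012 | 0.053 |
| 10 | 8.8 | 0.01 | 1.078 | 1.019 | 0.055 |
| 5 | 17.6 | 0.01 | 1.166 | 1.041 | 0.060 |
| 15 | 5.9 | 0.05 | 1.243 | 1.059 | 0.064 |
| 10 | 8.8 | 0.05 | 1.390 | 1.093 | 0.073 |
| 5 | 17.6 | 0.05 | 1.830 | 1.190 | 0.099 |
| any | – | 0 | 1.000 | 1.000 | 0.050 |

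For example, at k = 5 and ρ = 0.05: DE = 1 + 16.6 × 0.05 = 1.83, and R = √(2.83/2) = 1.190.

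**Do the planned terms already absorb this?** The formula above has no site, PCP or coach terms. I therefore repeated the comparison with all three in the working model and only the pharmacist left out. The layout was assumed: 175 patients, five sites, six PCPs per site and four coaches. Site, PCP and coach each had variance 0.01, pharmacists were nested in site, and coaches were assigned independently of pharmacists. For 15, 10 and 5 pharmacists, R was 1.012, 1.018 and 1.037 at ρ = 0.01, and 1.060, 1.088 and 1.169 at ρ = 0.05. The understatement is almost unchanged, and a little smaller with five pharmacists.

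**The case against.** The strongest reply is that nothing in the protocol shows pharmacist variance above zero. Pharmacists follow one standardised protocol and guideline algorithms under PCP guidance, which should limit differences between them, and the PCP is in the model. Grouping by pharmacist is also loose. Continuity is stated only under the MTMC item and only where possible, other faculty provide cover, and patients may decline the pharmacist and continue with the coach alone. The minimum is one pharmacist visit every six months, against monthly coach visits. At the only ICC in the document, the effect is 1–4%. All of this stands, and it limits the finding to a conditional one.

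A reader might infer four stronger things that the documents do not support:

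- That the standard error is too small. This needs a pharmacist variance that the coach term does not absorb, and no figure for it is given.
- That 15 pharmacists deliver mDAS. Fifteen caps the interviewees; the number delivering is stated nowhere.
- That pharmacists drive the medication changes. Changes are made under PCP guidance, and chart review counts both pharmacist- and physician-initiated ones.
- That pharmacist clustering is confined to mDAS. Usual-care patients are referred to a clinical pharmacist, so in year 1 it is mainly, not only, in the mDAS arm.

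It can also be said that the list is not closed, since subject is added later, and that an unseen SAP may complete it. A SAP that named the pharmacist would settle the matter. But section 12.0 chooses its provider levels explicitly, and subject is not a provider level.

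**Conclusion.** The omission is in the text, and it is inconsistent with the plan's own reason for modelling providers. The consequence is conditional: if outcomes cluster by pharmacist and the coach term does not absorb it, the reported standard error is too small. The two assumed inputs decide the size. At 0.01 with 10 to 15 pharmacists the excess is only about 1–2%; it becomes material with few pharmacists or an ICC nearer 0.05. Within the assumed range the error runs in one direction, towards intervals that are too narrow. This is a low-cost improvement to the analysis model, not a flaw that invalidates the design.

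**What to change.** In section 12.0, add the patient's primary study pharmacist to the list of random effects.

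- **Definition:** the first pharmacist seen, taken from the EMR visit notes.
- **Scope:** mDAS-period observations only. These are months 6 and 12 for the arm that starts with mDAS, and months 18 and 24 for the arm that starts with usual care. Baseline precedes allocation and carries no pharmacist effect.
- **Patients who never see a pharmacist:** state the coding in advance. Giving each such patient a separate level is simplest, but it depends on uptake after randomisation and should be acknowledged as such.
- **Inference:** Satterthwaite or Kenward-Roger degrees of freedom.
- **Fallback:** if pharmacists are too few for the component to be estimated, report the pharmacist model as a prespecified sensitivity analysis. Section 12.0 already allows a different approach for coaches when they are few.

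The cost is one more variance component, slightly wider intervals, and a component that may be estimated at zero. The pharmacist's identity must also be extracted: pharmacists write a note at each videoconference visit, but the planned chart review is described as collecting counts of encounters and medication changes, so identity would be an added item.

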### **Primary Outcomes**

Univariate comparisons between the two study groups for outcomes and covariates at baseline will be conducted using chi-square tests for categorical variables, Kruskal-Wallis tests for ordinal variables, and t-tests for continuous variables. Non-normal continuous data will be transformed prior to analysis.

In order to provide comprehensive analysis for  $H_1$ , we will extend the usual analysis of crossover designs by including a longitudinal trend component in the first year. Thus, we can examine the time course (0, 6, and 12 months) as linear or quadratic over the first three

measurements. This will allow us to investigate whether changes are made early, and at what rate they continue through the rest of the time period. This analysis permits the comparison of trends between the two conditions. In addition, we will regard subjects as a random effect and will use Gaussian mixed-model estimation (SPSS MIXED). We can then substitute treatment by period interactions for the carry-over effects, and the model can be reduced in a recommended sequence (first omit carry-over, then omit treatment, finally omit period). SPSS MIXED will also be used to explore patterned covariance structures such as compound symmetry and autoregression along with incorporating time-constant and time-varying covariates, such as health literacy or diabetes distress.

The primary analysis of all physiological outcomes jointly in the repeated measures design will be conducted in a general linear model framework. SPSS MANOVA (for repeated measures) will be used to explore the simultaneous impact of the treatment on multiple correlated dependent variables, including the use of Roy-Bargmann stepdown F-tests and discriminant function analysis as post hoc tests to identify subsets of outcome measures affected. MANOVA secondary analyses will explore the impact on results of inhomogeneous baseline variables. Group by time-trend interaction contrasts will be used to explore different group trajectories of change. The potential consequences of medication intensification (e.g., initiation of insulin) will be explored by evaluating changes in BMI and quality of life. Exploratory subgroup analyses will follow a heterogeneity in treatment effects (HTE) framework. We will determine which subjects in the intervention group had the greatest improvement in outcomes, based on multiple pre-specified patient characteristics, including race (African-American or Latino), depression, comorbidities, baseline behaviors, health literacy, continuity of care, and social support. These analyses will also consider additional comparisons between subjects above and below median levels of videoconferencing and text messaging activity. Statistical tests will be implemented as interactions within the full data set.

If the intervention is effective, we will examine whether changes in self-efficacy, health beliefs, or social support serve as mediators for improved outcomes according to our conceptual framework. In addition, we will explore diabetes-related behaviors as well as medication treatment intensification as mediators using MPlus. To further identify the relative contributions of videoconferencing and/or text messaging, we will conduct mediational modeling with videoconferencing time, number of text messages, and HC contact time as mediating variables. This may describe any dose-response relationships between mHealth utilization and outcomes. We will compute bias-corrected bootstrap standard errors using MPlus. This offers accurate confidence intervals for mediation coefficients. Due to anticipated relationships between HC activity level and mHealth delivery, we plan to inspect correlations between mediators and incorporate any significant findings in model development. This analysis will demonstrate whether intervention effects are sensitive to mediators. Finally, given the sample size, observed (rather than latent) variables will be used in the mediation models. To enhance the power of mediation modeling, we will adopt an  $\alpha=.10$  Type I error criterion to improve the chances of finding promising mediators for future study.

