## **6.0 Study Design and Procedures**

A randomized, controlled trial will evaluate the effectiveness of *mDAS* delivered by a clinical pharmacist and HC versus a usual care group. We will recruit 220 patients from UI Health. We recognize that all participants will have uncontrolled diabetes and require additional support from their healthcare team. Consequently, our usual care group will receive additional resources to meet basic standards of diabetes care and establish clinical equipoise between the two study groups. The usual care group will receive a referral to a diabetes educator and clinical pharmacist for medication reconciliation. These individuals are on staff and available to any patient, yet under-utilized. This group will receive a one-page contact sheet with the names and phone numbers of their local healthcare team as well as paper-based, low-literacy diabetes educational information. After one year, patients who have completed *mDAS* will be monitored for an additional year with usual care to evaluate maintenance, while the usual care patients receive *mDAS*. After recruitment, subjects will be randomized to receive either: (1) *mDAS* delivered by a clinical pharmacist and HC via home visits, videoconferencing, and text messaging; or (2) usual care. Study condition allocation will be completed after consent and baseline data collection. Using the REDCap Randomization Module, a random sequence of 220 subject assignments will be used. Blocked randomization (with varying block sizes) by clinical site, ethnic group (African-American and Latino), and gender will balance the proportion of participants.

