Sample Size Justification: Sample size calculations are powered to detect change in A1c. The ADA Technical Review of Diabetes Self-Management Education reported that successful education programs achieved reductions of 5-20% in A1c. The UKPDS 35 demonstrated that each 1% absolute reduction in mean A1c is associated with a 21% decrease in risk for any diabetes-related endpoint, a 21% decrease in diabetes-related deaths, a 14% decrease in risk for myocardial infarctions, and a 37% decrease in risk for microvascular complications. Based on our previous studies, we estimated a mean baseline A1c level of 10% with standard deviation of 1.8 and an effect size of  $(1.0/1.8) 0.56$  for Aim 1. The cross-time correlation was estimated to be 0.30 with compound symmetry structure. We adjusted for clustering and assumed an intraclass correlation coefficient (ICC) of 0.01 with five clusters. This yielded a design effect of 1.34. Two-sided alpha of 0.05 and 80% power were assumed. Allowing for 20% drop-out, 220 patients will be required total.

UI Health billing data show there are 7,258 adult African-Americans and Latinos with diabetes. We estimate that approximately half of these patients have an A1c level above 8.0% based on prior study. We anticipate recruiting 6% of the eligible diabetic population. We have successfully recruited a similar size of patients with type 2 diabetes using comparable recruitment methods.

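### The Aim 1 A1c analysis compares trends that start at month 0 without adjusting for baseline A1c or equating the arms there, and it admits covariates that treatment can change

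*Protocol*

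**What the plan says.** Section 12.0, Primary Outcomes, describes a Gaussian mixed model with a random subject effect for the first year. Month 0 belongs to the response: "we can examine the time course (0, 6, and 12 months) as linear or quadratic over the first three" measurements, and the stated purpose is to compare trends between the two conditions. The next paragraph plans a joint repeated-measures MANOVA of the physiological outcomes, with group-by-time-trend contrasts. Imbalanced baseline variables are left to secondary analyses. No passage names baseline A1c as a covariate or says that arm means are held equal at month 0.

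The mixed model will also be used for exploration, including "incorporating time-constant and time-varying covariates, such as health literacy or diabetes distress". Section 8.0 lists the DDS4, apparently the distress measure, in the outcome group collected at 0, 6, 12, 18 and 24 months.

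On design factors, section 6.0 states: "Blocked randomization (with varying block sizes) by clinical site, ethnic group (African-American and Latino), and gender will balance the proportion of participants". Section 12.0 adds that "we will include random effects in the model for clinic site, PCP, and HC". Section 8.0 lists gender and race/ethnicity among the baseline control variables.

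The sample size paragraph gives "mean baseline A1c level of 10% with standard deviation of 1.8", a difference of 1.0, and the statement "The cross-time correlation was estimated to be 0.30 with compound symmetry structure". It also "assumed an intraclass correlation coefficient (ICC) of 0.01 with five clusters", leading to a design effect of 1.34. "Two-sided alpha of 0.05 and 80% power were assumed", and 20% drop-out leads to 220 patients.

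**The concern.** In a randomised trial the arms have the same expected A1c at month 0, so a month-0 difference between them is chance. A trend comparison with free month-0 means estimates that difference and carries its noise into the treatment effect. When the correlation between visits is below 0.5, such a contrast is even less precise than comparing the 12-month values alone. The protocol plans on 0.30. At stake is power that the trial could have from a measurement it already takes.

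The covariate wording raises a separate issue. Distress measured after randomisation may respond to coaching and pharmacist support. Conditioning on it changes the question from the total effect of mDAS to the part that does not run through distress.

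**Working it through.** **Inputs from the protocol:** difference 1.0, SD 1.8, correlation ρ = 0.30 with compound symmetry, design effect 1.34, two-sided alpha 0.05, power 80%, drop-out 20%, N = 220. **Assumed:** 1:1 allocation, since no ratio is stated.

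**1. The protocol's own figures.** The design effect reproduces as 1 + (35 − 1) × 0.01 = 1.34, with about 176/5 = 35 completers per cluster. The total is N = 4 × (1.96 + 0.84)² × f × 1.8² / 1.0² × 1.34 / 0.80, where (1.96 + 0.84)² is 7.85 unrounded and f is the variance factor of the contrast:

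| Analysis | f | N |
|---|---|---|
| 12-month value only | 1 | 171 |
| Change or linear slope, month-0 means free | 2(1 − 0.30) = 1.40 | 239 |
| Baseline A1c as covariate | 1 − 0.30² = 0.91 | about 155 |

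None of these is 220. The nearest figure, about 225, needs the slope variance, the effect size rounded to 0.56, and inflation by 1.2 rather than division by 0.80. The powers below are therefore conditional on 220 randomised and a design effect of 1.34. Both analyses carry the same design effect, so their variance ratio does not depend on it.

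**2. Power in completers.** 220 × 0.80 = 176. Then 176/1.34 = 131 effective patients, or 65.7 per arm. SE = 1.8 × √(2f/65.7), and power = Φ(1.0/SE − 1.96).

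- Free month-0 means: f = 1.40, SE 0.372, power 76.7%.
- Baseline as covariate: f = 0.91, SE 0.300, power 91.6%.
- 12-month value only: f = 1, SE 0.314, power 88.9%.

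The ratio of the first two variance factors is 0.91/1.40 = 0.65. For three equally spaced visits under compound symmetry, the free linear trend has the same factor of 1.40 as the 0-to-12-month change.

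**3. Power using all available visits.** Assume 10% lost by month 6 (not in the protocol) and 20% by month 12. Generalised least squares with 110/1.34 effective patients per arm gives:

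- Free month-0 means, linear trend: SE 0.357, power 80.0%.
- Free month-0 means, categorical time: SE 0.358, power 79.8%.
- Month-0 means constrained equal, categorical time: SE 0.299, power 91.7%.

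The variance ratio is (0.357/0.299)² = 1.43. The like-for-like categorical comparison shows that the gain does not come from the choice of time scale. Moving the month-6 loss between 0% and 20% hardly changes these figures.

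**4. Sensitivity to the correlation** (0.5 and 0.7 are assumed; attrition as in step 3):

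| ρ | Free | Constrained |
|---|---|---|
| 0.30 | 80.0% | 91.7% |
| 0.5 | 90.8% | 95.9% |
| 0.7 | 98.8% | 99.4% |

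**5. Time-varying covariates.** The protocol has no figure from which to compute the share of the effect that runs through distress. As illustration only: if mDAS lowered distress by 0.3 SD, and A1c moved 0.3 SD per SD of distress, then 0.3 × 0.3 × 1.8 = 0.16 points would be adjusted away, or 16% of the 1.0 target. If 10%, 20% or 30% of the effect were removed (assumed shares), the 91.6% in step 2 would fall to 85.2%, 76.1% or 64.7%.

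**The case against.** The strongest reply is that the plan is valid and roughly meets its target. With all available visits, even free month-0 means give about 80%, which is what was planned. A more efficient analysis is then an improvement, not the repair of an error. This stands as far as bias is concerned: the trend comparison is unbiased. It does not remove the case for change, because the 80% needs an assumed attrition pattern and the completer figure is 76.7%.

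A second reply is that the text never says the month-0 means are free. That is correct, and the power loss is conditional on it. But a standard repeated-measures MANOVA contrast, which the next paragraph plans, estimates each arm's month-0 mean, and nothing in the protocol points the other way.

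Three stronger readings are tempting and should be resisted:

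- **That treating month 0 as an outcome is itself wrong.** It is not. A model with month 0 in the response and arm means constrained equal there has the same variance factor, 0.91, as covariate adjustment.
- **That two stratification factors are omitted and the standard errors ignore the design.** Site is in the model, gender and race/ethnicity are listed baseline control variables, and the time-constant covariate list is open. A full list may also belong to a SAP that is not shown.
- **That the main mDAS estimate will be biased toward zero by a known amount.** The covariate wording is exploratory, nothing says the main estimate will be adjusted for distress, and the 16% is a product of two assumed values.

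**Conclusion.** The point holds as one of efficiency and of covariate rules. With month-0 means free, power at the protocol's own inputs is about 77% (completers) to 80% (all visits, 10% loss by month 6 assumed), against about 92% with baseline adjustment or a constrained baseline. That is a gain of 12 to 15 percentage points from data already collected. It rests on the planned correlation of 0.30, falls to about 5 points at 0.5, and is below 1 point at 0.7.

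The covariate limb holds in principle. Section 8.0 itself separates baseline control variables from time-varying intermediate ones, and the mediation paragraph tests self-efficacy, health beliefs and social support as mediators. Yet the mixed-model text sets no boundary that keeps such variables out of the treatment-effect estimate. An effect adjusted for them would not be the total effect; the size of the difference is unknown.

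**What to change.** In section 12.0, Primary Outcomes:

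- For the Aim 1 A1c effect, model months 6 and 12 with categorical time, group-by-time and baseline A1c as covariate. Alternatively, keep month 0 in the response with arm means constrained equal. Report the adjusted 12-month difference.
- State how this estimate sits with the joint MANOVA, which is now called the primary analysis of the physiological outcomes. Keep the linear and quadratic trends as description.
- Restrict the treatment-effect model to baseline covariates. As a clarification, name the randomisation factors (site, ethnic group, gender) among them.
- Move time-varying distress and similar variables to the mediation analyses.

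The cost is analysis wording only: no new data, visits or patients.
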